### Main hypothesis

In women randomized to postpartum oral furosemide, in comparison to placebo:Daily averages of systolic, diastolic and mean arterial pressure (MAP) are lower, heart rate is the same and the frequency of very high blood pressure episodes is lower.Control of blood pressure is obtained earlier;Frequency of use of antihypertensive agent for the treatment of hypertensive crisis is lower, as well as the need for maintenance of antihypertensive therapy for blood pressure control;Fewer antihypertensive agents are needed in order to control blood pressure at hospital discharge;Time until blood pressure control is lower;Daily urine output is higher;Reduction of edema is obtained in less time;Length of hospital stay is reduced.

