However, even after birth and with appropriate treatment, concern about the complications of disease persist, since this condition can take days or weeks to resolve. In the postnatal period, with the return of liquid from the interstitial and extravascular compartment to the intravascular, very high blood pressure episodes are common and the persistence of hypertension in critical levels results in increased puerperal morbidity. Thus, blood pressure levels may continue to rise, which most often occurs in the first five days after birth, reaching a peak between three to six days after delivery [18]. New onset postpartum hypertension and preeclampsia can occur, with a frequency ranging from 0,3 %-27,5 % [19]. Complications of severe hypertension include stroke, eclampsia, congestive heart failure, acute pulmonary edema, renal failure and death [20].

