## Primary outcomes

Daily average of systolic, diastolic and mean arterial pressure (MAP);Heart rate;Frequency of very high blood pressure episodes.

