### Procedures for selecting participants and randomization

Eligible patients in labor will be invited to participate and those who agree and sign the informed consent form will be included in the study and then will be allocated to either using furosemide or placebo according to a random list of numbers generated by the Random Allocation Software Ispharan Iran, version 1.0. This list of randomization will be provided by the statistician to the pharmacist who will be responsible for preparing the packages containing either the furosemide or placebo, both in an identical presentation, with the identification number of list labeled. This procedure will be followed in order to guarantee the concealment of allocation of patients in both arms. Both patients and medical staff should be blind of the intervention condition in each case. Study medication and placebo, after delivered by the pharmaceutical industry to the pharmacy, will be packed as previously described and according the random list. The pharmacy will be responsible for sending sets to the ICU were the nurse in charge will keep all the packages until the administration of the drug to the patient according to the patients’ enrollment. The subjects will receive the study medication every 24 hours for a maximum of five days.

During the observation period the women will be subject to strict control of blood pressure, urine output (diuresis evaluated spontaneous or urinary catheter) and weight control. The routine management adopted at the hospital will be followed and other hypertensive agents will be initiated and chose according to the attending clinician's discretion.

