**Fig. 1 Fig1:**
[figure not shown]
Study design and population (CONSORT, 2010) [27]

The characteristics of the participants in each group will be compared with Student’s *t* test for continuous variables with normal distribution and Mann–Whitney U test for discrete and ordinal variables or those with non-normal distribution. Categorical variables will be compared with Pearson’s χ [2] test or Fisher’s exact test, as appropriate. P values for all tests will be two tailed at a 5 % level of significance.

Risk ratios and their 95 % confidence intervals will be calculated as a measure of relative risk. The number needed to treat (NNT) and its 95 % confidence interval will be calculated for the outcomes in which a beneficial effect of using furosemide is achieved, using the EBM calculator [http://moosenose.com/EBCalculator.htm]; in case of adverse effects the number needed to harm (NNH) and its 95 % confidence will also be calculated.

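### Daily blood pressure is a primary outcome with no fixed day or window, so if discharge follows recovery, comparisons after about day 2 are among women selected by an outcome of treatment

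*Protocol article*

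**What the plan says.** All references are to the protocol article.

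- **Endpoint.** Primary outcomes lists the daily average of systolic, diastolic and mean arterial pressure, heart rate, and the frequency of very high pressure episodes. No day, window or summary over days is named. Main outcomes defines the episode outcome as a daily number.
- **Expected effects.** Under Main hypothesis, on furosemide "Daily averages of systolic, diastolic and mean arterial pressure (MAP) are lower", "Control of blood pressure is obtained earlier" and "Length of hospital stay is reduced".
- **Setting.** Under Procedures for selecting participants and randomization, medication is given every 24 hours "for a maximum of five days". Women are monitored during an observation period whose end is not defined. Main outcomes measures hospital stay from the start of inpatient treatment to discharge. No discharge criterion, minimum stay or later pressure reading appears.
- **Analysis.** Data analysis plan commits to intention to treat. For continuous data it names Student's t "test for continuous variables with normal distribution and Mann–Whitney U test for discrete and ordinal variables or those with non-normal distribution".
- **Sample size.** The reference means are 142 (SD 13) and 153 (SD 19) mmHg. The Introduction gives these as postpartum day 2 values.
- **Time course.** The Introduction describes postpartum pressure as "reaching a peak between three to six days after delivery".

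**The concern.** A daily inpatient measurement is paired with a treatment expected to shorten the inpatient stay. If women go home because their pressure has settled, and are not measured afterwards, the later-day averages in each arm come from women who have not yet recovered. Who belongs to that group depends on treatment, so randomisation no longer protects the comparison. Intention to treat keeps each woman in her allocated arm, but it does not supply a reading for a day on which none was taken.

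At stake are the days when the protocol itself expects pressure to peak. Because no day is fixed, a day 3, 4 or 5 difference among remaining inpatients could be reported as a primary result.

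**Working it through.** **1. The plan's own figure.** For two means with unequal SDs:

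n per arm = (13² + 19²)(1.960 + 1.282)² / 11² = 530 × 10.51 / 121 = 46.0, rounded up to 47, so 94 in total.

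Allowing for 20 % loss, 94 / 0.80 = 117.5, or 118; the plan has 120. Both figures are acceptable. They describe a day-2 difference of 153 − 142 = 11 mmHg.

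**2. Model of discharge (assumed, not in the document).** Daily systolic pressure is normal with a constant true difference and correlation ρ between successive days. Discharge is possible from the end of day 2 for a woman whose pressure that day is below 140. All such women leave, or half of them each day.

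**3. Day 3 in closed form, all women below 140 leaving.** Selection raises the mean of those remaining by ρ·SD·λ, where a = (140 − mean)/SD and λ = φ(a)/[1 − Φ(a)]. The observed difference is the true difference plus the furosemide lift minus the placebo lift.

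| Assumption | SD·λ furosemide | SD·λ placebo | Day-3 difference, ρ = 0.5 to 0.8 |
|---|---|---|---|
| Means 139 and 150, SD 16 in both | 13.41 | 7.15 | −11 + 6.26ρ = −7.9 to −6.0 |
| Means 142 and 153, SDs 13 and 19 | 9.13 | 7.97 | −11 + 1.17ρ = −10.4 to −10.1 |
| Means 153 and 153, SDs 13 and 19 | 3.74 | 7.97 | 0 − 4.23ρ = −2.1 to −3.4 |

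The lift grows with the share of women removed, so it is larger in the arm with the lower mean. It also grows with the SD. With equal SDs only the first effect acts, and a true benefit shrinks. With the protocol's SDs the two nearly cancel. With no true difference in means only the SD effect is left to separate the arms, and it favours furosemide.

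**4. Day 5 by simulation (400,000 women per arm, constant means, ρ = 0.5 to 0.8, true −11 unless stated).**

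- SD 16, all below 140 leave: −7.6 to −5.6. Remaining: 21–30 % of furosemide and 50–59 % of placebo women.
- SD 16, half leave each day: −9.8 to −8.2.
- SDs 13 and 19, all leave: about −10.5 to −10.3.
- SDs 13 and 19, half leave: about −11.
- Discharge unrelated to pressure: −11.0.
- No true effect, both means 153, SDs 13 and 19: −2.5 to about −4 if all leave, about −1 to −3 if half leave.

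**5. Second set of assumptions** (means falling 3 mmHg a day, ρ = 0.3 to 0.8, true difference 11). The day-5 differences are:

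- Equal SD 16.3, all leave: 7.2 to 4.7, with power 25–28 % at 60 randomised per arm.
- Equal SD 16.3, half leave: 9.7 to 7.7, power 61–67 %.
- SDs 13 and 19, all leave: 10.2 to 9.8, power 49–85 %.

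With all 60 per arm measured, power for 11 mmHg is 96 %. Even where bias is small, the smaller numbers cost precision.

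Days 1 and 2 are unaffected in every case, because the model starts discharge at the end of day 2.

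**The case against.** Four objections carry weight.

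- **Restriction to inpatients is not stated.** A reader might infer that the plan compares only women still in hospital. No sentence says so. The full protocol or analysis plan may provide for readings after discharge, and silence in an article is not an error. This stands, and the point is therefore conditional. The inference is still reasonable: treatment is described as inpatient, urine output and complications are recorded during hospitalisation, and follow-up beyond discharge is described only for earlier trials.
- **Separate tests per day are not stated either.** The sentence on tests is introduced as comparing participants' characteristics and does not exclude a summary over days. This stands. However, it is the only method named for continuous data, and the endpoint is daily.
- **Direction and size rest on an invented discharge rule.** A reader might conclude that later differences are always pulled toward no effect, by 31 to 49 % on day 5 (1 − 7.6/11 and 1 − 5.6/11). The document does not support that. It gives no discharge criterion, and its recovery definition (all of at least four readings below 140 and 90 over at least 24 hours) is stricter than the rule modelled. Its own SDs bring the distortion down to about 1 mmHg or nothing. They can also produce a spurious benefit when the means are equal, so near-cancellation in one case is no assurance in general.
- **The comparison used for sizing is safe.** This stands: day 2 falls before the modelled discharge.

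**Conclusion.** The point holds in conditional form. The article leaves the day of a primary daily outcome open while expecting treatment to shorten the stay in which that outcome is measured. If discharge follows recovery and readings stop there, raw differences after about day 2 do not estimate the treatment effect.

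A true −11 mmHg on day 5 may appear as anything from about −5.6 to an undistorted −11 (−4.7 at the extreme of the falling-mean assumptions). A spurious −1 to −4 mmHg is possible when the SDs differ and there is no true effect. Neither a fixed direction nor a single percentage of attenuation can be claimed. The discharge pattern, the correlation and the trend over days are all assumptions. The day-2 comparison and the sample size are not in question. The change should be made; confidence is medium.

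**What to change.** 1. Name one primary blood pressure comparison in a fixed early window for all randomised women. Day 2 matches the source of the sample size, and systolic pressure is the measure used there. Say whether days run from delivery or from first dose, since the source figure is for postpartum day 2 and study treatment starts only after magnesium sulfate.
2. State whether pressure is measured after discharge and, if not, how those days enter the analysis.
3. Analyse later days with one likelihood-based repeated-measures mixed model with baseline pressure, arm, day and arm-by-day interaction. It is valid if discharge depends on recorded pressure and the model is correctly specified; discharge for unrecorded reasons related to pressure would break it. Given the reference SDs, let the variance differ by arm.
4. Do not present raw day 3–5 means or episode counts of remaining inpatients as treatment effects. Count very high pressure episodes over the same fixed early window for the primary comparison.

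The cost is a few sentences of analysis text, software that can fit a mixed model, and a missing-at-random assumption to be stated openly. No extra data are needed, provided that a pressure before the first dose is charted.

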## Methods/design

### Study design

The present study is a triple masked randomized controlled trial.

### Study population and location

The study population will comprehend all women hospitalized in IMIP during the data collection period with the diagnosis of preeclampsia/eclampsia.

### Eligibility criteria

Postpartum women diagnosed with severe preeclampsia, after completion of therapy with magnesium sulfate, with spontaneous diuresis and greater than 50 ml/h. Women with superimposed preeclampsia, or that used diuretics before admission to the intensive care unit (ICU), with acute or chronic kidney disease, diabetes mellitus; collagen disease; sickle cell anemia, patients with hemodynamic instability or with hypokalemia (K < 3.0 mEq/L) or patients with contraindications to the use of furosemide or unable to consent were excluded.

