In the systematic Cochrane Review that evaluated prevention and treatment of postpartum hypertension were included nine randomized clinical trials, of which two trials (282 women included) assessed postnatal furosemide at a dosage of 20-40 mg orally daily), compared with placebo or no treatment [25]. One trial added potassium supplementation (20 mEq orally daily) [23] and in the other [26] women at “high risk” of eclampsia also received magnesium sulfate. None of the studies reported the mean and standard deviation of the baseline blood pressure but one trial [26] reported a greater decrease in blood pressure in the group receiving furosemide compared to placebo. In the group receiving furosemide it was reported a change of blood pressure on days one, three and seven after delivery (i.e., −6.5 mmHg (furosemide) versus −3.5 (placebo) on day one, −10.6 (furosemide) versus −9.75 (placebo) on day three, and −11.5 (furosemide) versus −7.8 (placebo) on day seven). In the other trial [23] including 264 women, only postpartum patients with severe preeclampsia (*n* = 70) who received furosemide compared with controls had significantly lower systolic blood pressure by postpartum day 2 (142 +/− 13 mmHg compared with 153+/−19 mmHg, *P* < .004) and required less antihypertensive therapy during hospitalization (14 % compared with 26 %, *p* = 0.371) and at discharge (6 % compared with 26 %, *P* = 0.045). Follow-up ranged from day 10 postpartum [23] to six weeks postpartum [26].

The reviewers conclude that reliable data are not available to guide management of women with postpartum hypertension. For women with pre-eclampsia, postnatal furosemide may decrease the need for postnatal antihypertensive therapy in hospital, but more data are needed on substantive outcomes before this practice can be recommended. Notwithstanding, the optimal management of postpartum hypertension is not yet well established.

Thus, to determine the potential benefit of using diuretics in women with preeclampsia is an important issue in modern obstetrics. This study will be carried out with the objective of determining the effectiveness of furosemide to accelerate the recovery of hypertension in postpartum patients with severe preeclampsia.

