### Secondary maternal outcomes

Control of blood pressure;Frequency of use of antihypertensive agent for the treatment of hypertensive crisis;Need for maintenance of antihypertensive therapy for blood pressure control;Number of antihypertensive agents used to control blood pressure at hospital discharge;Time until blood pressure control;Daily urine output;Reduction of edema;Length of hospital stay;Adverse effects: hypokalemia, polydipsia, headaches, mental confusion, muscle aches, tetany, muscle weakness, heart rhythm disturbances and gastrointestinal symptoms;Frequency of maternal complications: imminent eclampsia, eclampsia, infection, bleeding manifestations, shock and maternal death.

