### Dependent variables

Daily maximum systolic blood pressure; daily maximum diastolic blood pressure; maximum average daily blood pressure; heart rate; frequency of very high blood pressure episodes; control of blood pressure; need for maintenance of antihypertensive therapy for blood pressure control; number of antihypertensive agents used to control blood pressure; time required for recovery of blood pressure; urinary output; length of hospital stay; adverse effects (polydipsia, headache, confusion, muscle aches, tetany, muscle weakness, heart rhythm disturbances, gastrointestinal symptoms); puerperal complications during hospitalization (acute pulmonary edema, hemorrhagic manifestations, imminent eclampsia, eclampsia, maternal death, shock, persistent edema.

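### Hypokalemia is listed as an adverse effect, missing from the variable list and given only a yes/no summary; comparing measured potassium would use the same data better

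*Protocol article*

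**What the plan says.** Four places in the protocol article bear on potassium as a harm.

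- **Secondary maternal outcomes** names it: "Adverse effects: hypokalemia, polydipsia, headaches, mental confusion, muscle aches, tetany, muscle weakness, heart rhythm disturbances and gastrointestinal symptoms". It is the only laboratory item in that list.
- **Dependent variables** gives the adverse effects again without it: "adverse effects (polydipsia, headache, confusion, muscle aches, tetany, muscle weakness, heart rhythm disturbances, gastrointestinal symptoms".
- **Eligibility criteria** excludes women with "hypokalemia (K < 3.0 mEq/L". This is the only potassium threshold in the article.
- **Data analysis plan** (text after Fig. 1) compares categorical variables by Pearson's chi-squared "test or Fisher’s exact test, as appropriate" and reports risk ratios. For harms it adds: "in case of adverse effects the number needed to harm (NNH) and its 95 % confidence will also be calculated". On the level, "P values for all tests will be two tailed at a 5 % level of significance".

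Main outcomes defines blood pressure, urine output and hospital stay, but not hypokalemia. No outcome or variable list contains serum potassium as a level or a change.

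**The concern.** There are two linked problems.

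1. The article contradicts itself on whether hypokalemia is analysed at all. It is an outcome in one list and absent from the matching list of variables.
2. If it is analysed, the only summary foreseen for adverse effects is a yes/no one. A cut discards the size of the fall and ignores where each woman started. Under any cut, a small fall just above it becomes an event, while a large fall that stops short of it does not.

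With about 60 women per arm, a count of uncommon events may say little about a drug effect that the potassium values themselves would show. At stake is how informative the trial is on the one laboratory harm it names. The primary conclusions are not affected.

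**Working it through.** **Inputs from the article.** 120 women in two groups (Sample size calculation), taken here as 60 per arm because the ratio is not stated; 94 before the loss allowance, so 47 per arm; two-sided 5 %; Fisher's test for sparse tables.

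**The plan's own figure.** It concerns systolic pressure only: n per arm = (13² + 19²)(1.960 + 1.282)²/11² = 46.02, rounded up to 47, so 94 in total. Allowing for 20 % losses, 94/0.8 = 117.5, close to the stated 120. The sample size therefore reproduces, and it was not set for potassium.

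**Assumptions, since the article gives no potassium figures.** On-treatment potassium is normal; placebo mean 3.8 or 4.0 mEq/L; SD 0.35, 0.4 or 0.5; furosemide lowers the mean by d. For the adjusted analysis, the correlation with entry potassium is 0.5. The cut of 3.5 is a second value for comparison only; it is not in the article and is not a proposal.

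**Formulas.**
- Event rates at cut c: placebo Φ((c − mean)/SD); furosemide Φ((c − mean + d)/SD).
- Fisher power: sum of the two binomial probabilities over all tables with p ≤ 0.05.
- Power for means: noncentral t with noncentrality d/(SD·√(2/n)).
- Adjusted for entry value: the same, with SD·√(1 − 0.5²).

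**One case in full** (mean 3.8, SD 0.4, d = 0.3, n = 60):
- Cut 3.0: Φ(−2.0) = 2.3 % v Φ(−1.25) = 10.6 %; Fisher power 28.9 %.
- Cut 3.5: Φ(−0.75) = 22.7 % v Φ(0) = 50 %; Fisher power 84 %.
- Means: noncentrality 0.3/(0.4·√(2/60)) = 4.11; power 98.3 %.

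**Range over the six mean and SD combinations, 60 per arm:**

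| True fall (mEq/L) | Count, cut 3.0 (Fisher) | Count, cut 3.5 (Fisher) | Mean potassium (t test) |
|---|---|---|---|
| 0.2 | at most 12 % | 26-57 % | 58-87 % |
| 0.3 | 0.2-34 % | 58-92 % | 90-99.6 % |
| 0.5 | 28-93 % | 98 % to nearly 100 % | essentially 100 % |

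Adjusting for entry potassium raises the power for means at a fall of 0.3 to 96 % or more. With 47 per arm and a fall of 0.3, Fisher power at 3.0 is 0.1-23 %, against 82-98 % for means.

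**Why the count is weak when events are rare.** With 60 per arm and no placebo events, 5 v 0 gives p = 0.057 and 6 v 0 gives p = 0.027. At least six events on furosemide are needed. With placebo mean 4.0, SD 0.4-0.5 and a fall of 0.3, about 2 to 5 would be expected below 3.0.

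**Where the gap closes.** For a fall of 0.5 and placebo mean 3.8, even the 3.0 cut has 89-93 % power; with mean 4.0 it has 28-66 %. At the 3.5 cut, a fall of 0.5 would be detected almost as surely by the count as by the means.

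**The case against.** **The cut may not be the outcome's.** A reader might infer that K < 3.0 mEq/L defines the on-treatment event, and so that the trial would probably report no difference even if furosemide clearly lowers potassium. The article does not support this. The figure stands in the exclusion criteria, and nothing carries it over to the outcome. The inference also needs a potassium mean, SD and effect that the article does not give, and it fails for larger falls with a low placebo mean. If any low value over up to five days counts as an event, events would be more frequent than one normal tail per woman suggests. This objection stands against the strong reading.

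**A condensed article leaves such detail elsewhere.** The threshold and laboratory schedule may be in a full protocol, and their absence is no fault. That also stands. It does not remove the conflict between the two lists, or the fact that the summary stated for adverse effects is a binary one. The t and Mann-Whitney tests are available in general, but no potassium variable is named for them.

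**Counting threshold events is conventional, and low power for a secondary harm is normal.** Both are true. They argue for keeping the count, not against adding the more informative comparison.

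**No safety conclusion is planned.** A reader might infer that a non-significant count would be presented as evidence of safety. The Discussion's description of furosemide as safe is background, and the planned confidence intervals would show how imprecise a sparse comparison is. Nor is it a defect that the article is silent on potassium supplementation, which the Introduction mentions for one reference trial.

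**Conclusion.** The point holds in a limited form. Two facts are firm on the text: hypokalemia appears in one adverse-effect list and not in the other, and adverse effects receive only a yes/no summary, with no stated outcome definition for this one.

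The inefficiency is real but its size is conditional. Under the stated assumptions and a fall of 0.3 mEq/L, the count has 0.2-34 % power at a cut of 3.0 and 58-92 % at 3.5, against 90-99.6 % for the means. The continuous comparison was more powerful in every scenario at falls of 0.2 and 0.3, so the recommendation does not depend on which cut applies. At 0.5 the advantage ranges from large to negligible. All potassium inputs, the normal model and the equal allocation are assumptions.

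This is a cheap improvement to a secondary safety analysis. It is not an error that threatens the trial's main result.

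**What to change.** 1. Reconcile Secondary maternal outcomes with Dependent variables so that hypokalemia is an analysed variable.
2. State the outcome definition of hypokalemia separately from the exclusion criterion. Which threshold to use is for the investigators.
3. Add a between-arm comparison of serum potassium during study treatment (lowest value, or change from entry) as a continuous variable adjusted for entry potassium, reporting the mean difference with its 95 % CI.
4. Keep the hypokalemia count with its risk ratio and number needed to harm.

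**Cost:** one extra analysis. An entry value is needed to apply the exclusion, and on-treatment values are needed to report hypokalemia as the secondary outcomes require. If the omission from the variable list means that on-treatment potassium was not going to be recorded, step 1 settles that first. No additional patients are needed.
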